**Table 4. Adverse Event Rates by Treatment Arm**

|                           | Placebo | 600mg |
|---------------------------|---------|-------|
| Individual AE Rate (AE 1) |         |       |
| ....                      |         |       |
| Individual AE Rate (AE k) |         |       |
| Overall AE Rate           |         |       |
| Overall AE Grade1         |         |       |
| Overall AE Grade 2        |         |       |
| Overall AE Grade 3        |         |       |
| Overall AE Grade 4        |         |       |

|                                                                |  |  |
|----------------------------------------------------------------|--|--|
| Overall AE Grade 5                                             |  |  |
| Overall AE not attributable to study drug                      |  |  |
| Overall AE (possibly or definitely) attributable to study drug |  |  |

**Table 5. Adverse Event Rates by Study Visits and Treatment Arm**

|                                                                | AEs Received by
Week 1 |        | AEs Received
after Week 1 till
Week 4 |        | AEs Received
After Week 4 till
Week 12 |        |
|----------------------------------------------------------------|---------------------------|--------|---------------------------------------------|--------|----------------------------------------------|--------|
|                                                                | PBO                       | 600 mg | PBO                                         | 600 mg | PBO                                          | 600 mg |
| Individual AE Rate (AE 1)                                      |                           |        |                                             |        |                                              |        |
| ....                                                           |                           |        |                                             |        |                                              |        |
| Individual AE Rate (AE k)                                      |                           |        |                                             |        |                                              |        |
| Overall AE Rate                                                |                           |        |                                             |        |                                              |        |
| Overall AE Grade1                                              |                           |        |                                             |        |                                              |        |
| Overall AE Grade 2                                             |                           |        |                                             |        |                                              |        |
| Overall AE Grade 3                                             |                           |        |                                             |        |                                              |        |
| Overall AE Grade 4                                             |                           |        |                                             |        |                                              |        |
| Overall AE Grade 5                                             |                           |        |                                             |        |                                              |        |
| Overall AE not attributable to study drug                      |                           |        |                                             |        |                                              |        |
| Overall AE (possibly or definitely) attributable to study drug |                           |        |                                             |        |                                              |        |

The safety analysis will be performed based on safety population. All randomized patients who have received at least one dose of study medication will be included in the safety analysis according to the treatment groups to which they are randomized.

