Concomitant medications will be recorded in terms of their daily dose, indication, and start and stop date. Study drug compliance will be monitored by pill counts of returned medication. In addition to the monitoring of individual patients at the local site, the study will be reviewed by the CSR&D Psychiatric, Behavioral Health & Neurologic Disorders Centralized Data Monitoring Committee.

Study participants will be monitored at each clinic visit (day 3, weeks 1, 4, and 12) and via telephone contact (weeks 2, 6, 8, and 10) by site investigators and coordinators for AEs and SAEs. Participants will be asked about any AEs or SAEs that have occurred since the previous visit or telephone contact, and vital signs will be obtained at all in-person visits. This frequent contact with participants, both in-person and via telephone, will enable site investigators to monitor safety, obtain PTSD symptom ratings, and identify any signs of deterioration. Information on all AEs and SAEs, including those related to the study intervention and those not related to the intervention, will be collected and recorded on the appropriate study event forms. All relevant information (e.g. onset of event, severity, outcome, extent to which it is or is not attributable to the drug or other study procedures) will be captured. Active monitoring of AEs and SAEs will begin as soon as a study participant signs the informed consent document and will continue through end-of-study for each participant. Instructions for contacting the VA National Suicide Hotline will be incorporated into the consent form and instructions for patients as part of safety monitoring. These safety data will be analyzed as described in the Analysis Plan (4.q.) and used to inform additional studies with mifepristone in the treatment of PTSD.

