##### 4.n.2. *Sample size determination*

As mentioned above, the sample size has been calculated to provide at least 90% probability that mifepristone 600 mg has been correctly identified as being superior to placebo if the population difference in response rate is at least 15%. Using the calculations provided by Simon et al. (1985) and accounting for a 20% attrition rate which has been reported in other drug studies using a similar population (Bartzokis et al., 2005), a total sample size of 90 is required, or 45 per treatment group. Since the sample size varies according to the responder rate (as well as the magnitude of the difference of interest), and the responder rate for placebo is unknown, we assume a placebo responder rate of 40%, which is at the high end of the studies referenced above. By contrast, in order to have a one-sided Type I error rate of 5% and 80% power to detect the 15% difference between two

groups using a traditional hypothesis testing framework, the study would require 274~344 participants when the placebo responder rate changes from 20% to 44%, after adjustment for a 20% withdrawal rate. If the true population difference in response rate is smaller than 15% (between 10~12%) and if we still consider it clinical significant, the proposed sample size (n=72 completers or 90 with 20% withdrawal rate) will still provide at least 80~85% probability of correctly identifying the superior group.

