Albuquerque has been one of the top recruitment sites for two CSP studies in PTSD: CSP 563 (“Prazosin and Combat Trauma”, having recruited 12 participants in 11 months) and CSP 504 (“Risperidone Treatment for Military Service Related Chronic PTSD”, 14 participants in 30 months). Recruitment was also high in other PTSD studies. However due to low recruitment in this study, this site was terminated in March, 2015. Salisbury and Little Rock were added in April 2015, instead, to help recruitment.

Salisbury VAMC was a very successful site for CSP 563 (“Prazosin and Combat Trauma”). It is also home to a MIRECC dedicated to the study of post-deployment mental health problems including PTSD and mTBI. It has a full research infrastructure and ready-access to the study group of interest.

Little Rock VA has just successfully recruited for and completed several studies of PTSD focused on a similar participant pool. One was a randomized controlled trial of modafanil in OEF/OIF combat veterans with PTSD (25 subjects completed the RCT over an 18 month recruiting period). [name], the site investigator, was also the collaborating psychiatrist on “Telemedicine-based collaborative care for posttraumatic stress disorder: a randomized clinical trial” and facilitated a study examining psychophysiological measures in OIF/OEF veterans.

We propose to enroll 90 participants across multiple VA sites to yield 72 completers based on an estimated attrition rate of 20%. We expect the 3 active sites (Bronx, San Diego, and Durham) to enroll 25~26 patients each over the course of 31 months (0.8 per site per month); and the 2 added sites (Salisbury and Little Rock) to enroll 5~6 patients each over the course of 9~10 months (0.5~0.6 per site per month). The Albuquerque site that was terminated in February 2015 enrolled a total of 2 participants.

Given the data provided by the VHA Support Services Center and the individual study sites, this recruitment goal, which takes into account the challenges of recruiting unmedicated veterans and stably medicated veterans, is feasible.

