#### Secondary Outcomes:

1. The analysis specified for the one-month responder rate will also be done for the three-month responder rate as a secondary analysis to check for the sustainability of the response.

Additionally, a continuous mixed-effects model for longitudinal observations of CAPS (past week symptom status) scores (week 1, 4 and 12) will be used. Covariates including baseline characteristics, specifically duration of symptoms, duration of illness since trauma, concurrent psychotropic medication use prior to randomization, overall extent of the psychiatric co-morbidity, military cohort, and site will be explored in the adjusted analysis. This analysis will provide a treatment effect in terms of the slope of the interaction term between group and time variables, conditional on aforementioned covariates under the missing at random (MAR) assumption (Laird and Ware, 1982).

The above mentioned analyses will be performed based on a mITT principle.

2. To describe the safety and tolerability mifepristone, information on all related and unrelated SAEs will be collected. There will be accelerated safety reporting for every two adverse events in every ten participants. The specific AE(s) leading to the withdrawal of a patient from study participation will be collected, along with characteristics of the AE including severity, duration, and whether the withdrawal was at the request of the patient or was initiated by a study investigator or other clinician. The AE rate will be determined on the basis of occurrence of at least one adverse event in each participant, and the following comparisons will be carried out:
  - a. A comparison of individual adverse event rates between mifepristone and placebo.
  - b. A comparison of overall adverse event rates between mifepristone and placebo.
  - c. A comparison of severity of adverse events (grades 1, 2, 3, 4, and 5) between mifepristone and placebo
  - d. A comparison of overall adverse event rates classified as possibly or definitely attributable to study drug, between mifepristone and placebo.
  - e. A comparison of overall adverse event rates classified as possibly or definitely attributable to study drug, between mifepristone and placebo by weeks 1, 4 and 12.

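### On plain reading, Table 5 keeps participants who have left the study in its later-interval adverse event denominators as event-free

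*Protocol*

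**What the plan says.** Section 4.p.1, Secondary Outcomes, item 2, defines the rate: "The AE rate will be determined on the basis of occurrence of at least one adverse event in each participant". Comparison (e) in the same item sets drug-attributable event rates side by side "between mifepristone and placebo by weeks 1, 4 and 12". The table shell headed "Table 5. Adverse Event Rates by Study Visits and Treatment Arm" has three columns that do not overlap, each split by arm: to week 1, after week 1 to week 4, and after week 4 to week 12.

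Directly below that shell stands the only population statement for safety: "All randomized patients who have received at least one dose of study medication will be included in the safety analysis", grouped by randomized arm. The protocol mentions no number at risk by interval, no person-time and no censoring for adverse events. Section 4.p.1 (Descriptive Outcomes) says that safety comparisons will be tested two-sided at 5%.

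On attrition, section 4.n.2 reaches 90 participants by "accounting for a 20% attrition rate which has been reported in other drug studies using a similar population", and the recruitment section repeats that 90 enrolled should yield 72 completers. Neither place gives the timing of loss or a split by arm, or says whether completion means week 4 or week 12.

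**The concern.** For a cumulative rate such as those in Table 4, dividing by everyone dosed is a normal convention. A rate for a separate later interval is different. Someone who left in week 2 is no longer seen at the scheduled visits and calls of weeks 4 to 12, so can hardly contribute an event there, yet under the stated population still counts in that column as event-free. The printed rate then falls below the risk among the people still being observed.

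The protocol itself foresees participants leaving. Section 4.h provides for premature exit during the treatment week. Item 2 of the safety analysis records events that lead to withdrawal from the study. The primary-analysis text describes participants found ineligible after randomization and terminated during the treatment week for safety; any of these who were dosed belong to the safety population but may have little later follow-up.

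The later columns are the only planned tabulation of how often events occur after the one-week pulse has ended. Comparing adverse events is a secondary objective, and section 4.i says the safety data will inform further studies of the drug.

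**Working it through.** **The plan's own figure.** 72 / (1 − 0.20) = 90 randomized, or 45 per arm; 90 × 0.80 = 72 completers, or 36 per arm. The stated numbers are reproduced.

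**Inputs.** Rate definition, interval limits and population: section 4.p.1. Attrition of 20%: section 4.n.2. The timing of loss is not in the protocol, so several timings are assumed. It is also assumed that the 20% is loss to adverse event follow-up among dosed participants, and that those who leave would have had the same event risk as those who stay.

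**Formula.** Let L(t) be the share of dosed participants lost by week t. To a close approximation, the relative understatement in an interval is the mean of L(t) over that interval.

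| Assumed timing of the 20% loss | Weeks 1–4 | Weeks 4–12 |
|---|---|---|
| Even over weeks 0–12, L = 0.20t/12 | 0.20 × 2.5/12 = 4.2% | 0.20 × 8/12 = 13.3% |
| Even over weeks 0–4, then none | 0.20 × 2.5/4 = 12.5% | 20% |
| All by week 1 | 20% | 20% |
| All after week 4, even over weeks 4–12 | 0% | 0.20 × 4/8 = 10% |

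**Check with an at-least-one-event model.** Take a constant event hazard within the interval and a true interval rate of 30%. Even loss over 12 weeks prints 28.8% for weeks 1–4 and 26.1% for weeks 4–12. Loss complete by week 4 prints 26.4% and 24.0%. The relative shortfalls are 4.0% and 12.9%, then 12.1% and 20%, in line with the table.

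**Comparison between arms.** If loss is complete before the interval and both arms have true rate p, the false difference is p × (difference in loss). With equal 20% loss and p = 30%, the table prints 24% against 24%, so the difference is zero. With an assumed 10% loss on placebo and 30% on mifepristone, it prints 0.30 × 0.90 = 27% against 0.30 × 0.70 = 21%, a false gap of 6 points. At 45 per arm that is 0.06 × 45 = 2.7 participants, against a standard error of √(0.27 × 0.73/45 + 0.21 × 0.79/45) ≈ 9 points.

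**What a start-of-interval denominator removes.** With even loss, 1 − 0.20 × 4/12 = 93.3% remain at week 4, and on average 86.7% are observed over weeks 4–12. Dividing by those present at week 4 gives 0.867/0.933 = 0.929, which leaves an understatement of about 7%. That removes roughly half of the 13.3%; the rest is loss within the interval and needs a person-time rate.

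**The case against.** The strongest reply is that no sentence states the Table 5 denominator. The population statement says who enters the safety analysis, the table is an empty shell, and column counts are often settled in an analysis plan, which is not shown here. This stands as a limit: the denominator is inferred. But rate definition, interval table and population are all in the protocol, and read together they point to one divisor, so this is more than a missing programming detail.

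The second reply is that the 20% is a sample-size allowance, not a forecast of lost safety follow-up. This also stands. It may include participants never dosed, who are outside the safety population. Section 4.e keeps participants taken off drug for an adverse event in follow-up, section 4.g does not require withdrawal after a treatment adjustment, section 4.h asks those who exit during treatment to return for assessment, and section 4.m.1 provides for unscheduled adverse event visits. A reader might infer that at most 36 of 45 per arm are observed after week 4. The protocol does not support that, because someone without a week 4 CAPS score can still report events.

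Three further inferences go too far. A reader might apply 13–20% to both later columns; for weeks 1–4 it is about 4% with even loss. A reader might conclude that the table creates a false arm difference; that needs unequal loss, which the protocol neither states nor assumes, and the 10% against 30% split is only an illustration. A reader might also object that columns of 1, 3 and 8 weeks cannot be compared; the headings show the limits, each column sets the arms against each other over the same interval, and no test across columns is planned.

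Finally, the trial is exploratory, enrolment pauses follow separate criteria in section 4.i, and no stated decision rests on the late columns. That lowers the stakes but does not make the divisor right.

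**Conclusion.** The point holds, with limited size. On plain reading, the later columns of Table 5 count participants who have left as event-free. If the 20% attrition is loss to adverse event follow-up, weeks 4–12 are understated by about 13% with even loss over 12 weeks and by 20% if all are lost by week 4 (10% if all loss comes evenly after week 4). Weeks 1–4 are understated by about 4% with even loss and by up to 20% if all are lost by week 1, or not at all if all loss comes after week 4. These are relative figures, and they shrink to the extent that the 20% includes never-dosed participants or people whose events are still collected. With equal loss in the two arms there is no false difference between them.

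A related ambiguity should be settled at the same time: the wording of comparison (e) can be read as cumulative, while Table 5 is by interval. The all-dosed denominator suits the first reading but not the second.

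**What to change.** For the second and third columns of Table 5, print by arm the number of dosed participants still in follow-up at the start of the interval and use it as the denominator. Because this corrects only loss before the interval, add a line giving participants with events, or events, per person-week of observed follow-up. Keep the all-dosed denominator for the cumulative rates in Table 4. State whether comparison (e) is cumulative to weeks 1, 4 and 12 or by interval, and match its denominator to that choice.

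The cost is one change of denominator and one added line per column, computed from the termination and contact records that the trial already collects. No new data are needed. The small downside is that the column counts will no longer equal the safety-population total, which a footnote can explain.

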#### 2.a.3. *Safety, tolerability and dosing*

The proposed study is grounded in the use of established clinical and experimental methods. In all previous studies of mifepristone in neuropsychiatric disorders, a pulse dose strategy has been employed with administration of mifepristone for 4-8 days. The majority of these studies used a dose of 600 mg/day (Belanoff et al., 2001; Belanoff et al., 2002; Young et al., 2004; Simpson et al., 2005; Gallagher et al., 2005; Flores et al., 2006; DeBattista et al., 2006; Blasey et al., 2009); 1200 mg/day has been studied in psychotic depression (Belanoff et al., 2002) and is being used in current studies of mifepristone in psychotic depression. In a recent Phase III trial of 600 mg/day of mifepristone in psychotic depression, a dose-response relationship between plasma concentration of mifepristone and treatment response was found. Only about one-third of the participants achieved what was previously determined to be the optimal blood level of mifepristone in depression. If a similar dose-response relationship exists in PTSD, some participants would need a higher dose of mifepristone to achieve clinical response; yet, in our pilot data there is preliminary evidence of a treatment effect at 600 mg/day. Accordingly, we will examine the effects of 600 mg/day of mifepristone and post-treatment mifepristone levels on clinical response. According to [name], rash is estimated to occur in 1% of persons treated with 300 mg/day of mifepristone, 3.3% of persons treated at 600 mg/day, and 5.5% of persons treated with 1200 mg/day (Corcept Therapeutics).

With respect to HPA axis activity, based on the results of the ACTH and CRF stimulation tests, pituitary and adrenal reserves are maintained during mifepristone treatment (Bertagna et al., 1994). Chronic treatment with mifepristone does not appear to be associated with the development of iatrogenic adrenal or pituitary insufficiency. Based on published reports and personal communication with [name] of Corcept Therapeutics, adrenal insufficiency has never been observed with one week of mifepristone treatment in depressed patients. (See also the section on monitoring adverse events, 4.i., for details on safety monitoring.) Nonetheless, since mifepristone is contraindicated in adrenal insufficiency, for safety reasons participants with a known history of this disorder or with low screening plasma cortisol levels will be excluded.

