#### 4.d.2. *Randomization Procedures*

Patients determined to be eligible and willing to participate in the study will be randomly assigned to 600 mg mifepristone or placebo using a web-based randomization system with a telephone call randomization system as back-up. The clinical research assistant at the participating facility will be required to sign into this password-protected site. The clinical research assistant will enter the patient study number and will be asked to answer a few questions about eligibility in order to complete the randomization procedure. If met, the website will select the first unused entry from the pre-specified list of random treatment assignments for the particular site and then assign a randomization number, which will be used to order the double-blind treatment prescription from the study site pharmacy. The randomization lists are stored on a secure server at Hines CSP Central Study File labeled "restricted access". A copy of appropriately executed and completed consent and HIPAA authorization documents must be on file at the Hines CSPCC within 24 hours of randomization, preferably before the patient is randomized. If the internet server is down during normal business hours, the clinical research assistant can telephone the Hines CSPCC to randomize a patient.

If a participant hasn't received the study drug on the day the participant is randomized, site coordinators should make every effort to ensure the participant receives the drug within 3 days post randomization, follows the directions on how to take the drug correctly, and that no study prohibited concomitant medications are used during this period. Should the study drug assignment program be down on any business day, site coordinators will contact the Albuquerque Pharmacy Center to request an emergency manual assignment.

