### **Description of Protocol Drugs:**

This is a Phase IIa trial of a medication that is approved by the FDA for termination of pregnancy, which results from its anti-progesterone activity and for the treatment of hyperglycemia in Cushing's Syndrome in patients who have failed surgery or are not candidates for surgery. It is being tested in this study since it is also an effective glucocorticoid receptor antagonist. This will be the initial trial examining the effects of mifepristone in PTSD. The CCTA study pharmacist will file an Investigational New Drug Application (IND) with the FDA, and if the IND is accepted by FDA, will serve as the Sponsor's Representative for the study. Mifepristone (Korlym®) 300 mg tablets and matching placebo tablets will be supplied to the study sites by the CSP Clinical Research Pharmacy Coordinating Center (PCC), packaged in bottles with safety caps. Each bottle will contain a seven-day supply as follows: 600 mg dose = fourteen 300-mg active mifepristone tablets; placebo dose = fourteen matching placebo tablets. Only one bottle will be required for each participant for the week of treatment, and will be labeled with a tracking identification number tied to a randomization number. No extra tablets will be included in the bottles. A supply of emergency bottles will be available at the sites for lost or damaged bottles, and will be assigned by contacting the PCC. Two tablets will be taken orally every evening with a meal. Participants who drop or in some way make unusable one or more tablets for a specific daily dose will be instructed to contact their site investigator the next morning. Adverse medical events will be assessed as outlined in the section on monitoring adverse events. Unused and expired drug will be disposed of as directed by the PCC.

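### The safety population is entered by exposure but grouped by randomised arm, so an adverse event after a dispensing error would be tabulated under the treatment not taken (minor)

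*Protocol*

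**What the plan says.** The definition stands in the protocol, section 4.p.1, in the paragraph after Table 5. Entry depends on exposure: "All randomized patients who have received at least one dose of study medication". Grouping depends on assignment: these patients "will be included in the safety analysis according to the treatment groups to which they are randomized".

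The adverse event comparisons under Secondary Outcomes, item 2, use these groups. They include "A comparison of overall adverse event rates between mifepristone and placebo" and comparisons by severity, by attribution to study drug and by period. Tables 4 and 5 are laid out by the same two arms.

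On supply, the Description of Protocol Drugs provides one bottle per participant for the whole week, which "will be labeled with a tracking identification number tied to a randomization number". There are two non-routine routes:

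- Under section 4.d.2, if the drug assignment program is down, "site coordinators will contact the Albuquerque Pharmacy Center to request an emergency manual assignment".
- Under Description of Protocol Drugs, "A supply of emergency bottles will be available at the sites for lost or damaged bottles". The same sentence goes on to say that these are assigned by contacting the pharmacy coordinating centre.

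No section gives a supplementary analysis by treatment received or a rule for a participant given the wrong product.

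**The concern.** Grouping by randomised arm protects the efficacy comparison, and the protocol already uses a modified intent-to-treat rule there. The safety question is different: what happened to people who took the drug. Under the stated rule, an event caused by mifepristone in a placebo-assigned participant who was given mifepristone would be counted as a placebo event. That would hold even in the Table 4 row for events attributable to study drug.

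Comparing drug-related adverse events between the groups is a secondary objective (section 1.c.2), and section 4.i says the safety data will inform further mifepristone studies. With arms of this size, a single misplaced event is visible in the table. The grouping cannot be treated as a detail left to the statistical analysis plan, because the protocol itself fixes it.

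**Working it through.** There is no stated figure to reproduce, because the point concerns a definition. The arithmetic only gives its scale.

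**Inputs**

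- Arm size: "a total sample size of 90 is required, or 45 per treatment group" (section 4.n.2).
- Scale of a safety signal: rash in "3.3% of persons treated at 600 mg/day" (section 2.a.3).
- Misdispensing rate: not given. The number misdispensed, k, is an assumption, shown for k = 0 to 3.

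**Step 1. No error (k = 0).** Assigned and received treatments coincide, so every count and denominator is the same under both groupings.

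**Step 2. One misplaced event.** One event in an arm of 45 is 1/45 = 2.2 percentage points. For comparison, rash expected among 45 treated is 45 × 0.033 = 1.5 cases.

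**Step 3. Illustration with assumed counts.** Suppose 3 of the 45 participants assigned to and given mifepristone have an event, and nobody given placebo does. Suppose also that k placebo-assigned participants were given mifepristone and every one of them has an event.

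| k | As randomised: active vs placebo | Difference (points) | As received: active vs placebo | Difference (points) |
|---|---|---|---|---|
| 1 | 3/45 = 6.7% vs 1/45 = 2.2% | 4.4 | 4/46 = 8.7% vs 0/44 = 0% | 8.7 |
| 2 | 3/45 = 6.7% vs 2/45 = 4.4% | 2.2 | 5/47 = 10.6% vs 0/43 = 0% | 10.6 |
| 3 | 3/45 = 6.7% vs 3/45 = 6.7% | 0 | 6/48 = 12.5% vs 0/42 = 0% | 12.5 |

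This is an upper-end picture, because every misdispensed participant is assumed to have an event.

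**Step 4. Expected effect instead.** Take rash at 3.3% on drug and assume no background rash. Then k misdispensed placebo-assigned participants add k × 0.033 expected cases to the placebo arm. For k = 1 the placebo rate rises by 0.033/45 = 0.07 points; for k = 3, by 3 × 0.033/45 = 0.22 points.

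**Step 5. Direction.** In the case of Step 4, everyone in the active arm still took mifepristone, so that arm's rate still estimates the rate on drug and only the placebo rate is distorted. In the opposite error, one active-assigned participant given placebo, the expected active-arm rate becomes 44 × 0.033/45 = 3.23% instead of 3.3%. That is also a shift of 0.07 points, now in the active arm only. If the drug raises the event risk, both errors bring the arms closer together.

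**The case against.** The strongest reply is that the design leaves little room for crossover. There is one bottle for the full seven-day course, with no extra tablets, no titration and no routine resupply. A reader might infer from the phrase about emergency bottles at the sites that site staff pick a replacement themselves. The rest of that sentence rules this out: the pharmacy centre assigns it. Manual assignment is likewise a request to the Albuquerque Pharmacy Center, and section 4.j.1 has the pharmacy coordinating centre preparing the code-envelopes for each randomisation number. The protocol reports no dispensing error, and deviations are tracked (section 4.1.3) and reviewed by the data monitoring committee (section 4.l.1). All of this stands. It makes an error unlikely but supplies no tabulation rule if one occurs.

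A second reply is that requiring one dose for entry while keeping randomised groups is coherent and close to the modified intent-to-treat rule. That is right. The definition does not contradict itself; it is a weaker choice for the safety question.

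A third reply concerns size. A reader might infer that one dispensing error costs 2.2 points, or hides most of a rash signal. The documents do not support that: the figure requires both a wrong bottle and an event in that same participant. Before the event is known, the expected shift is about 0.07 points for rash. Nor does a placebo-assigned participant who takes mifepristone lower the expected rate in the active arm.

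Finally, week-1 plasma mifepristone might seem to settle what each participant took. It cannot. The sample is drawn at one visit and will be missing for those who do not attend. Section 4.i also has medication stopped for rash or suspected adrenal insufficiency. A measurable level in a placebo-assigned participant is informative; an absent level in an active-assigned participant is not conclusive.

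**Conclusion.** The point holds as a minor, conditional one. The protocol fixes safety grouping by randomised arm and offers no as-received analysis, so an event after a dispensing error would be counted under the treatment not taken.

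The size is zero if no error occurs and about 2.2 points (1/45) in an arm's rate for each misdispensed participant who has an event. This assumes the planned 45 per arm all enter the safety population. The tendency to pull the arms together assumes that mifepristone raises the risk of the event in question. The documents do not support reading this as evidence that errors are likely, or that the safety comparison is materially biased as planned.

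**What to change.** In section 4.p.1, in the safety population paragraph after Table 5, replace the grouping by randomised arm with grouping *according to the treatment actually received*. Then add:

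- Treatment received is determined primarily from the bottle tracking number.
- Week-1 plasma mifepristone is a supporting check where available, read with the asymmetry described above.
- Any participant whose assigned and received treatments differ is listed.

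Leave the efficacy analyses by randomised arm. The cost is one phrase and a short listing. Tracking numbers and plasma samples are already part of the plan, so no new data are needed. The change is best made before unblinding.
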